### Statistical Analysis Methods

All analyses will be done under the intention-to-treat principle, where all randomized individuals will be included. Missing outcome data will initially be handled by a complete-case analysis, which assumes that data are missing at random (MAR). If data are systematically missing, then it may be the case that early responders differ from late responders and, in extension, that late responders are more similar to nonresponders. We will, therefore, explore the plausibility of the MAR assumption by regressing the primary outcomes on the number of follow-up attempts needed before a response was recorded. To further explore the MAR assumption, attrition will be investigated among study groups by comparing baseline characteristics between those who did and did not respond at follow-up. A sensitivity analysis that includes imputed values for missing outcome data (using multiple imputation by chained equations [58]) will also be performed. Data will be graphically examined for outliers or data input errors, and sensitivity analyses will be performed excluding any erroneous data points.

For all models, coefficients of interest will be assessed for statistical significance using a null hypothesis testing approach, where tests will be 2-tailed at the .05 significance level. Alongside the null hypothesis tests, posterior distributions using a Bayesian approach will be calculated for each coefficient. Both significance tests and posterior distributions will create a basis for scientific inference [59].

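### The plan says all randomised participants are included but starts from complete cases, and its one sensitivity analysis for missing outcomes, MICE, as standardly run rests on MAR again

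*Protocol article*

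**What the plan says.** All of this stands in the protocol article, Statistical Analysis Methods, unless noted.

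- Analysis set: "All analyses will be done under the intention-to-treat principle, where all randomized individuals will be included".
- Initial handling of missing outcomes: "Missing outcome data will initially be handled by a complete-case analysis, which assumes that data are missing at random (MAR".
- First check of MAR: "regressing the primary outcomes on the number of follow-up attempts needed before a response was recorded". The reason given is that, if data are systematically missing, it may be that "late responders are more similar to nonresponders".
- Second check of MAR: "attrition will be investigated among study groups by comparing baseline characteristics between those who did and did not respond".
- Sensitivity analysis for missing outcomes: "A sensitivity analysis that includes imputed values for missing outcome data (using multiple imputation by chained equations [58]) will also be performed". No departure from MAR is described.
- A further sensitivity analysis concerns data errors, not missing outcomes: "sensitivity analyses will be performed excluding any erroneous data points".

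The Power Calculation section needs 1800 analysed, assumes a mean response of 85% at 4 months and expects to lose 326 of 2126. Under Hypotheses, 2 months is the primary time point. Follow-Up Attempts sets the order of contact: web link, two reminders, questions by direct SMS, then up to five phone calls.

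**The concern.** The first two statements conflict. A complete-case analysis omits non-responders, so of the analyses described only the MICE analysis could include everyone randomised.

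The checks do not fully do the job given to them. A difference in baseline characteristics between responders and non-responders argues against MCAR, but it is what MAR would also produce. The attempts regression is better aimed. As described, though, it carries no adjustment, so heavier baseline drinkers who answer late would trigger it even if MAR held given baseline. Attempt number is also partly tied to mode of response.

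Whatever the attempts regression shows, no planned analysis takes it up. Arm-specific MNAR is not far-fetched here: participants know their allocation, only the intervention arm can disengage by sending STOP, and only controls get access to the tool after the final follow-up. The article itself discounts earlier trials for systematic attrition, so its own result should withstand the same question.

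**Working it through.** **1. The plan's own figures.** Using the distributions in Power Calculation and a Wald test on the log mean ratio, with variance (1/μ + 1/θ)/n per arm, average power at 1800 analysed is 0.791 (plan: 0.79). With response p following a beta distribution with mean 0.85 and SD 0.05, the mean of 1800/p − 1800 is 325, interquartile range 231 to 398 (plan: 326; 231, 398). The figures reproduce. The expected loss is 326/2126 = 15.3%.

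**2. How far from MAR before significance is lost.** Inputs from the plan: means 10 and 8.5 (a 15% reduction), θ = 1, 900 per arm, two-sided 0.05. Assumptions added here: the observed ratio is exactly 0.85, control non-responders are as MAR predicts, intervention non-responders drink k times the MAR prediction, and the SE is held fixed.

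- SE = √[(1/10 + 1)/900 + (1/8.5 + 1)/900] = √[(1.1 + 1.1176)/900] = 0.0496.
- Critical ratio = exp(−1.96 × 0.0496) = 0.907.
- With a fraction d missing, the all-randomised ratio is 0.85 × [(1 − d) + d·k].
- d = 0.10: 0.85 × (0.90 + 0.10k) = 0.907 gives k ≈ 1.67.
- d = 0.15: 0.85 × (0.85 + 0.15k) = 0.907 gives k ≈ 1.45.
- For the point estimate to reach 1.0 at d = 0.15: k = (1/0.85 − 0.85)/0.15 = 2.18.

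**3. What the planned checks and MICE would show.** This is an illustrative simulation on an assumed data model: 2126 randomised, 15% missing, 200 runs per scenario, true ratio about 0.85. Baseline drinking predicts outcome, and one latent tendency drives both late response and non-response. Imputation was by arm on baseline drinking.

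| Missingness | Full-data ratio | Adjusted complete case | Imputed | Attempts check significant, unadjusted | Same, adjusted for arm and baseline | Baseline check significant |
|---|---|---|---|---|---|---|
| MCAR | 0.848 | 0.849 | 0.849 | 0.09 | 0.10 | 0.06 |
| MAR on baseline drinking | 0.850 | 0.850 | 0.850 | 0.99 | 0.04 | 1.00 |
| MNAR, equal in both arms | 0.854 | 0.857 | 0.856 | 1.00 | 1.00 | 0.85 |
| MNAR, intervention arm only | 0.851 | 0.767 | 0.767 | 1.00 | 1.00 | 0.54 |

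Four things follow within this model:

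- The baseline check fires in every MAR run, where there is no bias, and in only 0.54 of runs where the bias is serious.
- The unadjusted attempts check cannot tell MAR from MNAR; adjustment for arm and baseline restores that distinction (0.99 falls to 0.04 under MAR).
- Even adjusted, it fires equally for symmetric MNAR (little bias) and arm-specific MNAR (large bias), which is the reason to add attempts by arm. That interaction was not itself simulated.
- Under arm-specific MNAR, complete case and imputation agree at 0.767 against 0.851. Their agreement is no reassurance.

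**The case against.** The strongest reply is that the plan does more than many. A reader might infer that MAR is examined only through a check that speaks to MCAR. The text does not support that: the attempts regression is aimed at outcome-related missingness, and only the baseline comparison fits the criticism. A reader might also infer that the attempts regression pools the arms. The article gives no specification either way, and a condensed article may leave one to the analysis plan. Nor can it be said that lateness and mode are inseparable, since attempts vary within the web stage and within the phone stage.

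The complete-case sentence is not wrong in itself. Adjusted models are primary, and an adjusted complete-case regression is valid when missingness depends only on covariates in the model. The baseline comparison also has a use for the unadjusted models, which need a stronger assumption. The MICE model is not specified, so useful auxiliaries are not ruled out.

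On size, the 85% response figure is for 4 months, while 2 months is primary and has no loss figure of its own; earlier trials with the same follow-up scheme exceeded 90%. The SE above is unadjusted, and the scenario places MNAR in one arm only.

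All of this stands and limits the point. What remains is on the page: the inclusion statement conflicts with complete cases, the baseline comparison is presented as exploring MAR, and no analysis described departs from MAR.

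**Conclusion.** The point holds in a limited form. The inclusion statement and the complete-case analysis need reconciling. Neither check can verify MAR: the baseline comparison cannot separate MAR from MNAR, and the attempts regression rests on late responders standing in for non-responders and, with no adjustment stated, would also signal under MAR. MICE as standardly run shares the MAR assumption, so a positive attempts check has no planned consequence.

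The size is illustrative. With an observed ratio of 0.85, an unadjusted SE of 0.0496 at 1800 analysed and controls at MAR, significance is lost when intervention non-responders drink about 1.7 times the MAR prediction at 10% missing, or about 1.45 times at 15%. Neither loss rate is the plan's figure for the 2-month primary time point. If MNAR is equal in both arms, the simulated bias is small (0.857 against 0.854). The documents therefore do not show that the trial's estimate will be biased, only that the plan describes no analysis that would reveal how sensitive the estimate is. This should be changed before analysis; it does not undermine the design.

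**What to change.** 1. Label the complete-case result as complete-case. Report MICE as the all-randomised analysis, with the other time point's outcomes and the 1-month mediators as auxiliaries.
2. Fit the attempts regression with arm, attempts by arm and the baseline covariates, and note when reading it that attempt number is partly tied to response mode.
3. Present the baseline comparison as a description of attrition, not as a test of MAR.
4. Add arm-specific delta-adjusted imputation, for example imputed consumption multiplied by 1.0 to 2.0, including scenarios that shift the intervention arm only, and report the tipping point.

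Cost: wording and some extra analysis code. Sample size, procedures and data collection are unchanged. The one downside is a wider reported range of results.

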#### Recruitment and Eligibility

Using Web search engine advertisements (Google, Yahoo, and Bing) and social media (Facebook), we will target individuals in the general population of Sweden seeking help to reduce their alcohol consumption (advertisements are shown in Figure 2). Participants will initially be recruited over a 6-month period. Additional 6-month periods will be added if not enough participants have been recruited according to the initial power calculation. If 20.03% (426/2126) or less of the required population has been recruited at 12 months, then recruitment will stop at this time and data will be analyzed to inform future trial design. Recruitment will stop after 24 months if not before.

Individuals interested in participating in the study will be asked to send an SMS message with a specific code to a dedicated phone number. Within 10 min, participants will receive an SMS with a hyperlink that takes them to a Web page asking for informed consent. Individuals will be randomized to 1 of 2 different means of presenting the trial procedure when asking for informed consent (Consent-1 and Consent-2). Please see Multimedia Appendix 1 for more details.

All individuals giving informed consent will be asked to complete a baseline questionnaire, which will also assess eligibility for the trial. The inclusion criteria will include the following: aged 18 years or older, ownership of a mobile phone, and being classified as a risky drinker according to Swedish guidelines.

Note that there is no upper limit to alcohol consumption as an exclusion criterion, meaning the study population is anticipated to comprise both harmful (ie, individuals who have experienced harm from any level of consumption [48]) and hazardous drinkers (ie, individuals with a consumption pattern that suggests increased risk to health [48]). No additional support will be offered to individuals who have a very high-consuming behavior.

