#### Randomization

In all cases, randomization will be fully computerized, will not employ any strata or blocks, and will not be possible to subvert as this and all subsequent study processes are fully automated. The main study will be single-blind as participants will be aware that 2 settings exist, and they will know which one of them they have been allocated to (intervention or control). The substudies involving Consent-1, Consent-2, Info-1, and Info-2 will be double-blind as participants will not be aware of the existence of the substudy or that they have been randomized. It is not possible to blind the individual responsible for data analysis, as this individual will also be responsible for data collection and involved in the monitoring of the technical platform.

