### Follow-Up Attempts

There are 3 follow-up stages: 1, 2, and 4 months after randomization. All follow-ups will be initiated by sending SMS messages to participants with hyperlinks to questionnaires. In all cases, the following attempts will be made to collect data from nonresponders:

A total of 2 reminders will be sent 2 days apart to those who have not responded.If no response is given to (1), then we will send questions directly in an SMS message, asking participants to respond directly with an SMS (no hyperlink).At 1 month, we will ask all 3 mediator questions.At 2 and 4 months, we will only ask for primary alcohol outcome measures.If there is no response given to (2), we will attempt to call participants to collect responses to the same questions as in (2). A maximum of 5 attempts will be made.

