### Power Calculation

We conducted a Monte Carlo simulation study to determine the necessary number of individuals to randomize (N). We deliberately focused on the total weekly consumption outcome, as the analysis of this outcome in general requires more individuals than does the analysis of heavy episodic drinking (because of higher variance). We will begin by describing the initial distributional assumptions that we made and then the result of the simulations. We aimed to achieve 0.8 power at the .05 significance threshold.

The effect (γ) of the intervention, that is, the percentage reduction in mean total weekly alcohol consumption in the intervention group, is assumed to follow a beta distribution with mean 0.15 and SD 0.025.The mean number of standard units consumed in the control group (μ_C_) at follow-up is assumed to follow a normal distribution with mean 10 and SD of 0.5. The population under analysis are risky drinkers, thus, a mean consumption of 10 standard units is appropriate, and the analysis is quite robust to moderate changes in this assumption.The mean number of standard units consumed in the intervention group (μ_I_) at follow-up is assumed to follow a normal distribution with mean (1-γ)_C_ and SD of 0.5.The distribution over the number of standard units consumed at follow-up for both the intervention and control group is assumed to follow a negative binomial distribution. The means of these distributions are given by μ_C_ and μ_I,_ respectively, and have a dispersion parameter θ sampled from a normal distribution centered at 1 with an SD of 0.05.The number of individuals allocated to the intervention group follows a binomial distribution, with a 0.5 probability of success over N trials.

The Monte Carlo simulation explored different values of N (number of individuals randomized). For each N explored, the following simulations were done:

Draw 1 sample each for γ, μ_C_, μ_I,_ and θAllocate a random number of individuals to the interventionGive each individual a number of standard units consumed following the negative binomial distribution appropriate for their respective groupsAnalyze the data using negative binomial regressionNote if the 0.05 threshold has been broken for the group allocation coefficient in the regression modelRepeat 100 times from (a) and then calculate power as the percentage of times that the threshold was brokenRepeat 1000 times from (1) and calculate the average power from (e)

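### Values judged to be input errors are, on the natural reading, left in the primary analysis and removed only in sensitivity analyses

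*Protocol article*

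**What the plan says.** The only sentence on wrong values is in Statistical Analysis Methods: "Data will be graphically examined for outliers or data input errors, and sensitivity analyses will be performed excluding any erroneous data points". The same section sets the analysis population: "All analyses will be done under the intention-to-treat principle, where all randomized individuals will be included". Missing outcomes are at first handled by complete cases.

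The section on hypotheses 1, 6 and 7 analyses weekly units and heavy-drinking frequency as counts by negative binomial regression, and makes the adjusted models primary.

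Other sections bear on how errors arise and who judges them:
- Under Measures, weekly consumption is one self-reported number for the past week.
- Under Follow-Up Attempts, people who do not answer two reminders are sent the questions by text message, "asking participants to respond directly with an SMS (no hyperlink"). Telephone calls come after that.
- Under Randomization: "It is not possible to blind the individual responsible for data analysis".

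**The concern.** The sentence places error handling in the secondary analysis. If the team has concluded that a number is a typing error, the headline estimate and its test should not contain it. As written they would, and the correct figure would appear only as a sensitivity result. If the two differ, the section does not say which one governs.

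Negative binomial regression copes with skewness and overdispersion, but it does not down-weight a single wild count in estimating the mean ratio. A large error in the intervention arm hides benefit, and the same error in the control arm creates it. The decision on what is erroneous also falls to an analyst who can know the allocation.

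**Working it through.** **Inputs.** From Power Calculation: control mean 10; a reduction that "is assumed to follow a beta distribution with mean 0.15 and SD 0.025", so a central intervention mean of 0.85 × 10 = 8.5; SD 0.5 on each mean; dispersion θ centred at 1 with SD 0.05; N = 1800, about 900 per arm; stated power 0.79. The target is "We aimed to achieve 0.8 power at the .05 significance threshold", and in Statistical Analysis Methods "tests will be 2-tailed at the .05 significance level". The size of a mistyped count is not in the documents. I assume one wrong value between 85 and 1000, recorded for a true value at the arm mean.

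**1. The plan's own figure.** For the log rate ratio, SE² = (1/μ_C + 1/θ)/(N/2) + (1/μ_I + 1/θ)/(N/2). Averaging the two-sided power over 200,000 draws of the reduction, both means and θ gives 0.791, against the stated 0.79. The expected loss to follow-up comes out at 325 (quartiles 231 and 398), against the stated 326 (231, 398). The design is reproduced.

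With every parameter fixed at its centre instead, SE = √[(1.1 + 1.1176)/900] = 0.0496, z = 0.1625/0.0496 = 3.27, and power is 0.91. That figure leaves out the uncertainty that the plan builds in, so it is not the plan's power.

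**2. Effect of one wrong count.** With a group term only, the fitted rate ratio equals the ratio of arm means. A count x recorded for a true 8.5 in the intervention arm gives μ_I = 8.5 + (x − 8.5)/900, and the reduction is 1 − μ_I/10. In the control arm, μ_C = 10 + (x − 10)/900, and the reduction is 1 − 8.5/μ_C.

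| Recorded x | Reduction, error in intervention arm | Reduction, error in control arm |
|---|---|---|
| none | 15% | 15% |
| 85 | 1 − 8.585/10 = 14.2% | 1 − 8.5/10.083 = 15.7% |
| 200 | 1 − 8.713/10 = 12.9% | 1 − 8.5/10.211 = 16.8% |
| 700 | 1 − 9.268/10 = 7.3% | 1 − 8.5/10.767 = 21.1% |
| 1000 | 1 − 9.602/10 = 4.0% | 1 − 8.5/11.1 = 23.4% |

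**3. What halving would need.** On the percentage scale, μ_I must reach 9.25, so x = 8.5 + 0.75 × 900 = 683.5. On the log scale, μ_I must reach 10 × √0.85 = 9.2195, so x = 8.5 + 0.7195 × 900 = 656.

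**4. Check with fitted models.** In 150 simulated trials, negative binomial fits gave these estimated reductions with one intervention-arm error:

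| Recorded x | Unadjusted | Adjusted for log baseline consumption |
|---|---|---|
| none | 14.9% | 14.9% |
| 85 | 14.1% | 14.0% |
| 700 | 7.2% | 6.6% |
| 1000 | 3.9% | 3.5% |

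The simulated baseline is an assumption. Adjustment, which the plan makes primary, gives no protection.

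**5. Would the error be seen?** With mean 8.5 and θ = 1, P(Y > k) = (8.5/9.5)^(k+1). The median of the largest of 900 genuine values is then 64. A recorded 85 is not far beyond that, whereas 700 is about eleven times as large. At 12 g per unit, 700 units is 8.4 kg of alcohol in a week.

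No figure is given for heavy episodic drinking, because the documents state no mean for it.

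**The case against.** The protocol does not say outright that confirmed errors stay uncorrected in the primary analysis. Querying and range checks usually sit in a data management plan or SAP, and the questionnaires are in an appendix that is not shown. With an unblinded analyst, keeping discretionary exclusions out of the headline result is itself a safeguard. Any error large enough to matter would be plain on the planned plot, and its influence would show in the planned re-analysis.

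Much of this stands. The absence of form limits or query steps is no finding. The safeguard argument is sound for doubtful values, but weaker for values shown to be wrong, and it falls away once those are settled without sight of allocation. That the error would be obvious supports the change, because a value known to be wrong has no place in the primary estimate. Nor does intention to treat require keeping it: correcting a number removes nobody, and setting it to missing puts that person with the other missing outcomes.

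A reader might infer two further faults that the text does not support:
- **Heavy drinkers and typing errors treated alike.** The plan looks for both outliers and errors, but excludes only erroneous points.
- **Unlimited follow-up entries.** The statement that "there is no upper limit to alcohol consumption as an exclusion criterion" concerns eligibility, not what the forms accept.

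**Conclusion.** The point holds as a stated rule in the wrong place. Exclusion of erroneous values is assigned to sensitivity analyses alone, so on the natural reading the primary result contains them. That reading is an inference, though no other rule is offered.

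The size depends on an assumed error. A one-digit slip in one record costs under one percentage point of a 15% reduction. A single value of 700 to 1000 brings it down to about 7% to 4%, or, at 1000 in the control arm, up to about 23%.

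A reader might infer that any single mistyped count can halve the effect, or that power would fall from 0.91 to about 0.35. The documents do not support either as a general claim. Halving needs roughly 656 to 684 units or more, in the intervention arm, with 900 analysed per arm. The 0.91 comes from fixing parameters that the plan draws from distributions, and the plan's own power is 0.79.

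**What to change.** Replace the sentence in Statistical Analysis Methods with a rule to this effect:

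*Before the primary analysis, reported weekly units and heavy-drinking occasions will be checked against a plausibility rule fixed in advance. Flagged values will be settled without sight of allocation. Values shown to be impossible or mistyped will be corrected where the intended value can be established, and otherwise set to missing. Genuine extreme values will be kept. A sensitivity analysis will use all values as received.*

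Because the analyst also runs data collection, the flagged values should be settled by someone else, from a listing that omits allocation. The plausibility limits can go in the SAP, provided that they are set before outcome data are seen by arm.

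The cost is a few lines of text and a short review. The small downside is that a few values become missing.

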**Methods:**

A 2-arm parallel group randomized controlled trial will be employed to estimate the effect of the novel intervention. Participants will be recruited through Web advertisements and social media. The inclusion criteria are as follows: 18 years or older, ownership of a mobile phone, and being classified as a risky drinker according to Swedish guidelines. Participants allocated to the intervention group will receive a novel mHealth intervention. The intervention consists of weekly screening, personalized feedback on current consumption, functions allowing for planning of future consumption, as well as a series of messages delivered throughout the week. Participants allocated to the control group will receive a short message regarding negative consequences of alcohol consumption and a hyperlink that offers more information. Following 2 and 4 months after randomization, both groups will be asked to complete follow-up questionnaires (2-month interval being primary). Primary outcomes are weekly alcohol consumption and heavy episodic drinking. Participants in the control group will be given access to the novel intervention after completing the 4-month follow-up. The trial includes 3 substudies: We will explore whether the mode of presenting information before participants giving informed consent affects participation rates and recall of trial parameters, investigate if the content of the short message received by the control group affects study outcomes and requests for more information, and explore user satisfaction with the intervention and reactions of the control group.

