### Measures

All questions asked at baseline and subsequent follow-ups can be found in Multimedia Appendix 3.

For hypotheses 1, 6, and 7:

Primary outcome measures: Total weekly alcohol consumption and frequency of heavy episodic drinking.Secondary outcome measures: Classification as risky drinker according to Swedish guidelines.

For hypothesis 2:

Mediation measures: Confidence in one’s ability to reduce consumption, importance of reducing, and knowledge of how to reduce consumption.

For hypotheses 3 and 4:

Primary outcome measures: Enrollment rates from each study conditionSecondary outcome measures: Recall of trial procedures measured through a series of questions.

For hypothesis 5:

Primary outcome measures: Rates of additional information being requested by pressing on the supplied hyperlink.

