**Main Hypotheses**
1. Alcohol consumption will differ between intervention and control groups, with the intervention group drinking less than control at 2 and 4 months after randomization. The 2-month interval will be primary.2. Confidence, importance, and know-how at 1-month follow-up will mediate the effects of the intervention on drinking outcomes at 2-month follow-up. The same measures at 2-month follow-up will mediate the effect on drinking outcomes at 4-month follow-up.3. Enrollment rates will differ between groups Consent-1 and Consent-2.4. Accurate recall of study parameters will differ between groups Consent-1 and Consent-2.5. Rates of accessing further information will differ between groups Info-1 and Info-2.

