#### Baseline

Baseline characteristics will be compared among the different groups using chi-square tests or Fisher exact tests for comparison of proportions and Mann-Whitney *U* tests for comparison of means.

#### Hypotheses 1, 6, and 7

Total weekly alcohol consumption and frequency of heavy episodic drinking are likely to be skewed and overdispersed, and we will, therefore, analyze both using negative binomial regression. Classification as a risky drinker will be analyzed using logistic regression. Both unadjusted and adjusted regression models will be created. Adjusted models will include baseline values of the respective outcome measures and responses to the baseline questions regarding sex, civil status, age, motivation, importance, and know-how. As alcohol consumption differs significantly among age groups, and possibly also the effect of the intervention, multilevel models will also be created in which slopes are allowed to vary among age groups. Effect modification tests will be performed in all models to assess if any of the baseline characteristics moderate the effect of the intervention. The adjusted models will be the primary models.

#### Hypothesis 2

Mediators will be explored using a causal inference framework [60], where Monte Carlo methods are relied upon for inference. This allows for any type of model (linear and nonlinear) to be used to represent the relationships between the group allocation, mediating variable, and outcome. A total of 4 models will be created for each outcome measure, 3 that investigate the mediating factors on their own and a fourth that incorporates all mediators at once. If any baseline characteristics were found to moderate the effect in the primary analysis, then additional mediator models will be created to include these as moderators.

#### Hypotheses 3 and 4

Whether or not individuals decided to give informed consent will be regressed against group allocation (Consent-1 and Consent-2) using logistic regression. Adjusted regression models will be explored that include baseline characteristics (including only participants who gave informed consent). Differences among the 2 groups on responses to the recall questionnaire will be investigated using chi-square tests or Fisher exact tests for comparison of proportions.

#### Hypothesis 5

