### Limitations

The trial is designed to recruit enough participants to power the main alcohol-related outcomes; thus, the included substudies are not powered to detect significant differences. Rather, the substudies included herein are supposed to be seen as preliminary and exploratory work laying a basis for future trials of these phenomena.

The power calculation considers a range of follow-up rates (beta distribution with a mean of 85% and an SD of 5%), and the number of individuals (n=2126) found to be necessary to randomize may have to increase toward the upper quartile (n=2198) if follow-up rates are found to be lower than the mean of 85%. Our previous trials [24,65] have been able to collect data from more than 90% of participants using the same follow-up scheme used in this trial; thus, despite not using incentives to sustain high levels of follow-up rates, we believe our expectation of 85% follow-up rate to be warranted.

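### Two primary outcomes are each tested at .05 for one hypothesis with no order, alpha split or either/both rule, so a 5% error rate for hypothesis 1 is not secured

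*Protocol article*

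**What the plan says.** The Methods paragraph of the Abstract names two primary outcomes: "Primary outcomes are weekly alcohol consumption and heavy episodic drinking". The Measures section repeats them for hypotheses 1, 6 and 7: "Primary outcome measures: Total weekly alcohol consumption and frequency of heavy episodic drinking".

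Both outcomes serve a single main hypothesis, worded for alcohol consumption in general: "Alcohol consumption will differ between intervention and control groups, with the intervention group drinking less than control at 2 and 4 months after randomization". The article narrows the primary family in two ways. It fixes the time point, "The 2-month interval will be primary", and, under Statistical Analysis Methods for hypotheses 1, 6 and 7, it fixes the model, "The adjusted models will be the primary models".

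For error control, Statistical Analysis Methods sets one rule for every model: "coefficients of interest will be assessed for statistical significance using a null hypothesis testing approach, where tests will be 2-tailed at the .05 significance level". Bayesian posterior distributions are to be reported beside the tests and share in the inference, but they have no decision threshold. The Power Calculation section sizes the trial on weekly consumption alone, at the full .05.

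No section orders the two primary tests, divides alpha between them, or says whether hypothesis 1 needs one or both to be significant.

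**The concern.** The article settles the time point and the model but leaves open how the two outcomes combine. That leaves exactly two primary tests, each at two-sided .05, bearing on one claim. Under an either-outcome reading there are two chances of a false positive, and the rate for the claim exceeds the nominal 5%.

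The Randomization section says that the person who analyses the data cannot be blinded. Without a rule set in advance, the outcome that carries the claim could be settled after the results are known. The choice also affects the design: the sample size spends all of .05 on weekly consumption, so a later alpha split would lower the power on which the trial was sized.

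**Working it through.** **Inputs from the article.** Two primary outcomes; two-sided .05 for each; one primary time point and one primary model, so two primary tests. From Power Calculation: a reduction with a beta distribution (mean 0.15, SD 0.025), a control mean that is normal (10, SD 0.5), an intervention mean that is normal around the reduced control mean (SD 0.5), dispersion θ normal (1, SD 0.05), binomial 1:1 allocation, N=1800 analysed.

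**Assumed input.** The correlation ρ between the two test statistics. The article gives none, so a range is shown.

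**Step 1: reproduce the stated power.** The test statistic is log(μ_I/μ_C) divided by its standard error, √[(1/μ_C + 1/θ)/n_C + (1/μ_I + 1/θ)/n_I]. Averaging two-sided power at .05 over the article's distributions gives 0.791. A full simulation with negative binomial data and estimated θ gives 0.794. The article states 0.79. The stated loss to follow-up of 326 (interquartile range 231 to 398) reproduces as 325 (231 to 398). The sizing calculation is therefore not in question.

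**Step 2: familywise error if either outcome suffices.**
- Independent tests, both directions: 1 − (1 − 0.05)² = 0.0975.
- Independent tests, benefit only: 1 − (1 − 0.025)² = 0.0494, against 0.025 for one test.
- Correlated tests, both directions: 1 − P(|Z1| < 1.96 and |Z2| < 1.96) for a bivariate normal.
- Correlated tests, benefit only: 1 − P(Z1 < 1.96 and Z2 < 1.96), with Z signed so that positive means benefit.

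| Assumed ρ | Any false positive (two-sided) | False claim of benefit | Two-sided with .025 each |
|---|---|---|---|
| 0 | 9.75% | 4.9% | 4.9% |
| 0.3 | 9.5% | 4.8% | 4.8% |
| 0.5 | 9.1% | 4.5% | 4.7% |
| 0.8 | 7.8% | 3.9% | 4.0% |
| 0.9 | 7.0% | 3.5% | 3.6% |
| 1.0 | 5.0% | 2.5% | 2.5% |

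**Step 3: error if both outcomes are required.** The chance that both are falsely significant cannot exceed the chance for either one, so it is at most 5%. Power to succeed on both cannot exceed the 0.79 for weekly consumption. The article gives no joint power.

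**Step 4: what each remedy does to power for weekly consumption.** With weekly consumption first in a fixed sequence, it is still tested at .05 and power stays at 0.79. At .025, power at N=1800 falls to 0.74, and a power of 0.80 would need between 2200 (0.787) and 2400 (0.806) analysed. Holm lies between: weekly consumption is tested at .05 when heavy episodic drinking is significant at .025, and otherwise at .025, so its power is between 0.74 and 0.79.

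**The case against.** The strongest reply is that the either-outcome rule is inferred. The article does not say that one significant outcome confirms hypothesis 1, and it bases inference on posterior distributions as well as tests. A reader might infer a flat statement that the trial's false-positive rate is 8% to 10%. The documents do not support that. The inflation depends on the either-outcome reading; 10% is only the upper bound for any dependence; and the rate is below 8% once the correlation passes about 0.77. Heavy drinking occasions add to weekly units, so a positive correlation is plausible. The recall windows differ (last week against the past month), so its size is unknown.

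A reader might also take the two-sided figure as the chance of falsely declaring the intervention effective. It is not: it counts false harm too. The rate for false benefit is about half of it.

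A third reply is that a condensed article may leave the decision rule to a fuller document. Both outcomes are named in advance, and a fixed sequence would be compatible with the .05 wording. This weighs on severity and does not remove the point: the article states .05 for all models and uses all of it in the sample size, and followed as written it does not hold the claim to 5%. The posterior distributions supply no error control, because no threshold is attached to them.

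Finally, the labelling of hypotheses 3 to 5 (listed as main, while Limitations says that "the substudies included herein are supposed to be seen as preliminary and exploratory work") does not enter the figures above. It is a separate and minor inconsistency.

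**Conclusion.** The point holds in conditional form. With two primary outcomes each at two-sided .05 and no rule joining them, the text permits a claim on either. Under that reading the two-sided familywise error is about 7% to 9.75%, and the chance of a false claim of benefit about 3.5% to 4.9% against 2.5%, for assumed test-statistic correlations from 0.9 down to 0. The excess disappears only at a correlation of 1. If both outcomes were required, the error would be at most 5% and the loss would be in power. The defect is that the article does not say which reading applies. It should be fixed; it does not invalidate the design, and the stated power calculation stands.

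**What to change.** State the decision rule for hypothesis 1 before outcome data are seen. One suitable rule is a fixed sequence at 2 months in the adjusted models: weekly consumption, on which the trial was sized, at two-sided .05 first, then heavy episodic drinking at .05 only if the first is significant. This takes a few sentences, needs no more participants and leaves the stated 0.79 unchanged.

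Its cost is that heavy episodic drinking cannot be claimed alone if weekly consumption misses, which happens in about 1 − 0.79 = 21% of trials on the design assumptions. That is a real price, since Power Calculation says heavy episodic drinking generally needs fewer participants. Holm avoids it, with power for weekly consumption between 0.74 and 0.79 at N=1800 analysed; the sentence fixing .05 for all models would then need amending. If both outcomes are to be required, say so and give the joint power.

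Under any rule, describe the 4-month, risky-drinker, multilevel and effect-modification tests as supportive. As a minor point, bring the main label of hypotheses 3 to 5 into line with the Limitations section.
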